### 2.7. Sample Size Determination and Statistical Analysis

The proportion of metastatic lesion specimens that meet NOP analysis criteria is expected to be approximately 70%. The proportion of primary lesions that meet NOP analysis criteria is likely to be lower than the 63.6% reported by Hisada et al. because of the reduced number of passes in the PRIMATE study. In addition, in our previous retrospective study, the proportion of primary tumor specimens obtained by EUS–TA with a 19G needle meeting criteria on pre-check was 53.8%, with a median number of punctures of four. Therefore, the proportion of primary lesion specimens that meet NOP analysis criteria in the present study is expected to be approximately 45%. Accordingly, the minimum sample size required for a Fisher’s exact test is 56 patients, assuming a one-sided significance level of 0.05 and a power of 80%. Assuming that approximately 10% of registered patients will experience difficulty in puncturing, a sample size of 61 patients is planned.

The proportion of EUS–TA specimens meeting NOP analysis criteria will be compared between primary and metastatic lesions using Fisher’s exact test. Statistical significance is set at *p* < 0.05.

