## Abstract

**Simple Summary:**

Although comprehensive genomic profiling (CGP) has attracted attention in unresectable pancreatic cancer with metastasis, the success rate of CGP in specimens obtained by endoscopic ultrasound-guided tissue acquisition (EUS–TA) is not high. This study is expected to improve the success rate of CGP of unresectable pancreatic cancer with metastasis in the future by clarifying whether the optimal target of EUS–TA is primary or metastatic lesions.

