The procedure is terminated once two specimens each are obtained from primary and metastatic lesions, after confirming by EUS and endoscopy that there are no findings suggestive of hemorrhage. If bleeding is suspected, endoscopic hemostasis or endovascular treatment will be considered.

Specimens obtained by EUS–TA are thinly sliced after formalin fixation and stained with hematoxylin and eosin. Specimens, excluding those from the ROSE session, are checked to determine whether they meet NOP analysis criteria. The sample volume required for NOP analysis is five 10 μm thick sections, with tumor cellularity of ≥20% and total DNA content of ≥200 ng per slide. A tissue area of approximately 16 mm^2^ per slide is recommended; however, a tissue area of 4 mm^2^ or more yields > 200 ng of total DNA. Therefore, we consider specimens with tumor cellularity of ≥20% and a tissue area of ≥4 mm^2^ as successfully meeting NOP analysis criteria. The pathological evaluation is performed by two pathologists, and any discrepancies in the measurements are resolved by discussion. In this evaluation, tumor cellularity is evaluated at five levels (>80%, 60–80%, 40–60%, 20–40%, and <20%), and tissue area is evaluated at four levels (≥25, 16–25, 4–16, and <4 mm^2^).

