## 4. Conclusions

In clinical settings, the first choice for the target of EUS–TA in UR–M pancreatic ductal adenocarcinoma is the pancreatic primary lesion. However, the success rate for meeting CGP analysis criteria is not high in specimens acquired from the primary lesion because one characteristic of pancreatic ductal adenocarcinoma is low cellularity. If this study finds that the percentage of metastatic lesion specimens meeting NOP analysis criteria (trial examination) exceeds the percentage of primary lesion specimens meeting the criteria (standard examination), metastatic lesions should be recommended as the target of EUS–TA when considering CGP in UR–M pancreatic ductal adenocarcinoma. This may allow more patients with UR–M pancreatic ductal adenocarcinoma to benefit from CGP. It may be possible to eliminate the conventional two-step procedure of EUS–TA for the primary lesion for diagnosis and percutaneous liver biopsy of the metastatic lesion for CGP. With their incorporation into future guidelines, the results of this study may change the standard for selecting targets for EUS–TA in pancreatic ductal adenocarcinoma with metastatic lesions.

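### The 80% power holds for a one-sided 0.05 test, but the analysis sentence gives p < 0.05 with no side; read as two-sided, the planned Fisher test has about 70% power

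*Protocol article*

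**What the plan says.** All the statistical text is in section 2.7 of the protocol article.

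- **Planning rates.** For metastatic lesions: "The proportion of metastatic lesion specimens that meet NOP analysis criteria is expected to be approximately 70" per cent. For primary lesions, the proportion of specimens that "meet NOP analysis criteria in the present study is expected to be approximately 45" per cent.
- **Sizing.** "the minimum sample size required for a Fisher’s exact test is 56 patients", "assuming a one-sided significance level of 0.05 and a power of 80" per cent. Allowing for about 10% of patients with difficult puncture, 61 are planned.
- **Analysis.** The next paragraph names Fisher's exact test again. It then says "Statistical significance is set at" p < 0.05, with no side and no direction.

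The aim is worded openly. The Simple Summary speaks of "clarifying whether the optimal target of EUS–TA is primary or metastatic lesions", and the Introduction says it is not yet known which lesion does better. Section 4 (Conclusions) describes the consequence in one direction only: if the metastatic percentage "exceeds the percentage of primary lesion specimens meeting the criteria (standard examination), metastatic lesions should be recommended as the target of EUS–TA".

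Section 2.6 shows that the data are paired: "The procedure is terminated once two specimens each are obtained from primary and metastatic lesions" in each patient.

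**The concern.** The one-sided level appears in the sizing sentence and is not carried into the analysis sentence, so the plan does not fix the rule for its only primary comparison. An unqualified p < 0.05 is usually read as two-sided, and a two-sided test also suits a question that is open in both directions. The 80% power was computed for the one-sided test alone.

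Two things are at stake. Under a two-sided reading, the trial has less power than the article states. And while the side is open, a result in the borderline zone can be called positive or negative depending on a choice made after the data are seen. Section 4 expects the result to be able to change which lesion is targeted as standard, so the rule should be settled in advance.

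**Working it through.** **Inputs (section 2.7).** p1 = 0.45 (primary), p2 = 0.70 (metastatic), difference d = 0.25, alpha 0.05 one-sided, power 80%, Fisher's exact test. Each patient supplies both lesions, so 56 patients means 56 results per lesion type, counting one result per lesion per patient. The 61 planned less 10% is 54.9, or about 55.

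**Step 1: reproduce the plan's figure.** With mean rate 0.575:

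n' = [z_α √(2 × 0.575 × 0.425) + z_β √(0.45 × 0.55 + 0.70 × 0.30)]² / d²

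One-sided: [1.645 × 0.699 + 0.842 × 0.676]² / 0.0625 = 47.3, so 48 without continuity correction.

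With the correction, n = (n'/4)[1 + √(1 + 4/(n'd))]² = 55.

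Exact enumeration of Fisher's test over two independent binomials gives one-sided power of 80.2% at 55 and 81.4% at 56. The stated 56 is therefore sound on its one-sided inputs. The same formulas with z = 1.960 give 61 and 68, so the plan's figure did not come from a two-sided calculation.

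**Step 2: the same test at two-sided 0.05.** Exact enumeration, 45% v 70%:

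| Evaluable per lesion | One-sided 0.05 | Two-sided 0.05 |
|---|---|---|
| 55 | 80.2% | 68.8% |
| 56 | 81.4% | 70.1% |
| 61 (no losses) | 84.4% | 76% |
| 68 | – | 79.7% |
| 69 | – | 80.4% |

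Two-sided Fisher first reaches 80% at 69 per lesion, before any allowance for failed punctures.

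**Step 3: can the side change the verdict?** Take primary 25/56, close to the planned 45%:

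| Metastatic | One-sided p | Two-sided p |
|---|---|---|
| 35/56 (62.5%) | 0.044 | 0.088 |
| 36/56 (64.3%) | 0.029 | 0.057 |

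Both results are positive under the sizing sentence and negative if the analysis sentence is read as two-sided. Both metastatic rates lie only modestly below the planned 70%.

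**Step 4: a two-sided paired test at the present size.** The document gives no within-patient correlation, so phi is an assumption and is varied. The probability that both lesions qualify is p11 = p1·p2 + phi·√(p1(1−p1)·p2(1−p2)). The discordant probabilities are b = p2 − p11 (metastatic only) and c = p1 − p11 (primary only). Power is summed over the binomial number of discordant pairs out of 56.

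| Assumed phi | b | c | Exact McNemar | Mid-p McNemar |
|---|---|---|---|---|
| 0 | 0.385 | 0.135 | 69.4% | 74.9% |
| 0.2 | 0.339 | 0.089 | 79.5% | 84.2% |
| 0.3 | 0.317 | 0.067 | 85.4% | 89.3% |

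A two-sided paired test can thus recover about 80% at 56 pairs if the lesions are modestly positively correlated, but not if they are uncorrelated.

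**The case against.** The strongest reply is that the article states only one sidedness. It declares one-sided 0.05, then names the same test and the same 0.05 a few lines later, and nowhere says two-sided. On that reading the level carries over and the sentence is merely incomplete. This stands in part: it is an omission, not a contradiction between two stated levels. But the text does not say that the level carries over, and the omission governs the one primary comparison.

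A one-sided test can also be defended. Section 4 treats the primary lesion as the standard examination and the metastatic lesion as the trial examination, and the planning rates point the same way. If only a metastatic advantage would change practice, a one-sided test fits that decision. This stands, provided that the direction is written down and the limit on the conclusion is accepted.

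The 70% belongs to an unpaired two-sided Fisher test, and a paired analysis may do better. That also stands: Step 4 shows it, subject to an unknown correlation.

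A reader might go further and infer that section 4 sets a separate rule, under which metastatic lesions are recommended on any numerical excess without a test. The document does not support this. The sentence is closing prose about what a positive result would mean, and the natural reading is that it refers to the comparison set in section 2.7. No error rate should be attached to a rule that the plan does not set.

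**Conclusion.** The point holds as an unfixed side, not as an arithmetic error. The 56 is right for one-sided 0.05 Fisher (81.4%). Under the usual reading of the analysis sentence, the same test has about 70% power at 56 per lesion, 69% at 55, and 76% with all 61 evaluable.

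These figures assume true rates of 45% and 70%, one result per lesion per patient, and, for Fisher, independence between lesions. The paired figures rest on assumed correlations of 0 to 0.3; a negative correlation would give less power than the values at zero.

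It would be too strong to say that the plan specifies a two-sided test and is underpowered for it, or that a one-sided test is wrong here. The document supports neither. It leaves open which test its 80% has to serve, and that choice can decide the outcome on plausible data.

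**What to change.** Before analysis, state one rule for the primary comparison in section 2.7.

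- **Preferred:** a two-sided 5% paired test, naming either exact or mid-p McNemar, because both lesions come from the same patient. Restate power at 56 pairs as about 69–75% if the lesions are uncorrelated, 80–84% at an assumed phi of 0.2 and 85–89% at 0.3, and say that the correlation is not known.
- **Alternative:** keep one-sided 0.05, write the side and direction (metastatic greater than primary) into the analysis sentence, and state that superiority of the primary lesion cannot then be concluded. The aim in the Simple Summary should be worded to match.

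In either case, word the recommendation in section 4 as depending on that test.

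The cost is wording, plus, under the preferred option, a power statement that may be less favourable than 80%. No extra patients and no change to procedures are needed.

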The relationship between the EUS–TA technique and the percentage of successful CGP analyses has also been evaluated. Park et al. reported that the puncture needle diameter (22G or 19G) and tumor site (body–tail), but not needle type (fine needle aspiration or FNB), contributed to a successful CGP analysis of primary pancreatic specimens collected using EUS–TA [30]. Larson et al. reported that large FNB needle diameter (19G, *n* = 2; 22G, *n* = 41; and 25G, *n* = 2) was associated with a high success rate for meeting NGS analysis criteria (*p* = 0.05) [28]. Therefore, when performing EUS–TA with an FNB needle for CGP, a large puncture needle diameter, with a large amount of tissue sampled, is recommended to achieve a high analysis success rate.

However, the optimal puncture target remains controversial. Larson et al. compared the proportion of specimens that met CGP criteria between those obtained by EUS–TA for primary pancreatic lesions or percutaneous biopsies for metastatic lesions and found a significantly higher success rate for metastatic lesions than for primary lesions, despite the difference in sampling modalities (*p* = 0.036) [28]. Ikeda et al. reported that, overall, 39.2% (60/153) of pancreatic specimens obtained with an FNB needle met NOP analysis criteria during pre-check; however, primary lesion specimens (37.1%, 53/143) were significantly less likely than metastatic lesion specimens (70%, 7/10) to meet analysis criteria (*p* = 0.049) [31]. Nevertheless, data on the proportion of metastatic lesion specimens that meet CGP analysis criteria remain insufficient, and it is not yet clear whether primary or metastatic lesions have a high success rate for CGP analysis of invasive pancreatic adenocarcinoma.

Therefore, we designed a study to clarify the appropriate target for EUS–TA when CGP is planned for pancreatic ductal adenocarcinoma by comparing the success rates for meeting NOP analysis criteria between primary and metastatic lesion specimens obtained during the same EUS–TA session in patients with invasive pancreatic ductal adenocarcinoma. The protocols are described herein.

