### 2.2. Study Design

This is an ongoing single-center prospective self-controlled trial. The study flowchart is shown in Figure 2.

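### The primary comparison is planned and tested with Fisher's exact test for independent groups, although each patient supplies both lesions; under positive within-patient correlation this miscalibrates the p-value and wastes power

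*Protocol article*

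**What the plan says.** Section 2.2 describes the design: "This is an ongoing single-center prospective self-controlled trial". The Introduction says that the study compares "primary and metastatic lesion specimens obtained during the same EUS–TA session in patients with invasive pancreatic ductal adenocarcinoma". Section 2.6 adds that "The procedure is terminated once two specimens each are obtained from primary and metastatic lesions".

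Section 2.7 then sets out the planning. For metastatic lesions, "The proportion of metastatic lesion specimens that meet NOP analysis criteria is expected to be approximately 70" percent. Primary lesion specimens that "meet NOP analysis criteria in the present study is expected to be approximately 45" percent. On that basis "the minimum sample size required for a Fisher’s exact test is 56 patients", "assuming a one-sided significance level of 0.05 and a power of 80" percent. An allowance of about 10% for difficult punctures brings the plan to 61 patients. In the analysis paragraph, the proportions "will be compared between primary and metastatic lesions using Fisher’s exact test".

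The article mentions no paired method, no within-patient correlation and no expected share of discordant patients.

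**The concern.** Each patient with both lesions punctured yields a primary result and a metastatic result, so the data are matched binary pairs. Fisher's exact test treats them as two unrelated samples of 56. Its null distribution is right for this design only if the two lesions of a patient are uncorrelated. In a paired comparison the information lies in the discordant patients (one lesion meets the criteria and the other does not), and the sample size makes no assumption about how many there will be.

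This is the only test named for the only primary question, and the Conclusions section says that the result may change how puncture targets are chosen. A test that discards the benefit of self-control is more likely to miss a real difference. Switching to a paired test after the data are seen would look post hoc.

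**Working it through.** **Inputs.** From section 2.7: 45% (primary), 70% (metastatic), one-sided 0.05, 80% power, 56 patients. Assumed: the within-patient correlation phi, which the documents do not give, and a null rate of (45% + 70%)/2 = 57.5% in both lesions for the type I error. The working treats each lesion as giving one yes/no result.

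**Step 1: reproduce the plan's figure.** Exact one-sided Fisher power for two independent binomial groups at 45% and 70%:
- 54 per group: 79.2%
- 55 per group: 80.3%
- 56 per group: 81.4%

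The stated 56 reproduces to within one patient as the size of *each* of two independent groups.

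**Step 2: put the pairing in.** The probability that both lesions meet the criteria is

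p11 = 0.45 × 0.70 + phi × √(0.45 × 0.55 × 0.70 × 0.30) = 0.315 + 0.228 phi.

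Only the metastatic lesion meets them: 0.70 − p11 = 0.385 − 0.228 phi. Only the primary lesion meets them: 0.45 − p11 = 0.135 − 0.228 phi. The discordant share is the sum, 0.520 − 0.456 phi. The largest possible phi is 0.135/0.228 = 0.59. At phi = 0.3 the discordant share is 0.520 − 0.137 = 0.383.

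**Step 3: behaviour of the two tests on 56 correlated pairs.** Fisher's rejection region was enumerated over the joint distribution of the pairs. Exact McNemar power was enumerated over the number of discordant pairs.

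| phi | Discordant share | Fisher type I error | Fisher power | Exact McNemar power |
|---|---|---|---|---|
| −0.3 | 0.657 | 5.6% | 78.3% | 71.5% |
| −0.2 | 0.611 | 4.9% | 79.2% | 74.5% |
| 0 | 0.520 | 3.5% | 81.4% | 80.9% |
| 0.2 | 0.429 | 2.1% | 84.1% | 88.2% |
| 0.3 | 0.383 | 1.5% | 85.7% | 92.0% |
| 0.5 | 0.292 | 0.5% | 89.8% | 98.4% |

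At phi = −0.1 Fisher's type I error is about 4.2%. It crosses 5% near phi = −0.25, where it is 5.2%. The type I error of exact McNemar stays between 2.9% and 3.7% over the tabulated range.

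**Step 4: pairs needed for 80% power with exact McNemar.** 65 at phi = −0.2, 55 at 0, 45 at 0.2, 40 at 0.3 and 31 at 0.5.

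**Step 5: a constructed example with strong correlation.** Take 56 patients: 24 meet the criteria in both lesions, 12 only in the metastatic lesion, 3 only in the primary, 17 in neither. The margins are 36/56 and 27/56.
- phi = (24 × 17 − 12 × 3)/√(36 × 20 × 27 × 29) = 372/750.8 = 0.50.
- Fisher: one-sided p = 0.064 (two-sided 0.127).
- Exact McNemar: P(12 or more of 15 at ½) = (455 + 105 + 15 + 1)/32,768 = 0.018 one-sided (two-sided 0.035).

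The same data fall on opposite sides of 0.05 depending on the test.

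**The case against.** The strongest reply is that the choice does little harm. With positive correlation, the natural expectation when two lesions share a patient and a session, Fisher's test errs on the safe side, so a significant result would still be trustworthy. At the planned rates its power is at least 81% for every non-negative phi tabulated, so the 80% target is met. That stands, and it limits the point to calibration and efficiency.

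Four stronger readings are tempting, and the documents support none of them:
- *The p-value is invalid whichever way the correlation goes.* Under positive correlation it is conservative, which is a different fault from failing to control false positives.
- *Any negative correlation inflates the error.* At phi = −0.1 and −0.2 the type I error is still below 5%. The excess appears only near −0.25 and is small, and nothing in the article suggests a correlation of that kind.
- *The figure of 56 can only come from an unpaired design.* Exact McNemar at phi = 0 also needs 55 pairs. The supportable criticism is that Fisher's test is the stated basis and no discordance assumption is given.
- *The conclusion would typically reverse.* The example has phi of about 0.50, close to the maximum of 0.59 at the planned rates, and a difference of 9/56 = 16 points rather than the planned 25. At about the planned effect (39/56 vs 25/56) Fisher gives one-sided p = 0.006, so there is no reversal.

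It may also be said that an unseen analysis plan could settle this. That would excuse silence, but section 2.7 names the test twice. A last objection is that McNemar needs one outcome per lesion, whereas two specimens are taken and section 2.3 words the endpoint by specimen. That is correct, and the fix has to deal with it.

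**Conclusion.** The point holds as a mismatch between test and design in the primary analysis. Section 2.7 fixes an independent-groups test for paired binary data and takes its power from the same test.

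The size depends on a correlation that the documents do not give. For phi between 0.2 and 0.5, Fisher's type I error is 2.1% down to 0.5% against a nominal 5%, and its power is 4 to 9 percentage points below exact McNemar on the same patients. At phi = 0.3 the chance of missing the planned difference is 14% instead of 8%; at 0.5 it is 10% instead of 2%. At phi = 0 the two tests are practically equal. Below zero Fisher has the higher power, and from about phi = −0.25 it gets there partly by exceeding its nominal error.

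A reader might infer that the trial is too small or that its false-positive risk is inflated. Neither is shown for phi of 0 or above. The correction is needed because the test is wrong for the design, it bears on the sole primary question, and it has to be fixed before the data are analysed. All figures assume 56 complete pairs, the planned rates, a one-sided 0.05 level as in the sample-size sentence, and one outcome per lesion.

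**What to change.** In section 2.7, and in the analysis plan if there is one:
- Replace Fisher's test with an exact or mid-P McNemar test on one outcome per lesion per patient.
- State how the two specimens of a lesion form that outcome. If specimens are to be counted singly, use a method clustered by patient instead.
- State how a patient with only one lesion successfully punctured enters the paired comparison, since about 10% puncture difficulty is expected.
- Report the within-patient difference in proportions with a confidence interval for paired data.
- Keep the sample size, and restate power for the paired test over a range of correlations. For exact McNemar with 56 pairs and one-sided 0.05 this is 74.5% at phi = −0.2, 81% at 0, 88% at 0.2 and 92% at 0.3. The figure below 80% at negative phi should be shown openly.

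The cost is a rewording of the sample-size and analysis sentences plus a definition of the lesion-level outcome. No extra patients, procedures or data are needed.

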## 3. Discussion

This study will play an important role in determining the target of EUS–TA in pancreatic cancer with distant metastases when CGP analysis is considered. However, there are several limitations. First, the study will not randomize the initial lesion to be punctured and will allow for the same needle to be used to puncture the primary and metastatic lesions, which may have an impact on EUS–TA as the needle tip gradually deteriorates over time, making specimen collection more difficult. However, the primary and metastatic lesions will be punctured alternately after the first lesion is punctured. Changing the puncture needle at the discretion of the physician when they sense needle deterioration will be allowed. These make this the least confounding factor.

The second is the EUS–TA method. The usefulness of wet suction has been reported in recent years [33,34,35,36,37,38,39,40,41,42,43], with better quality specimens obtained compared with those obtained by dry suction. However, in the meta-analysis, the specimen adequacy rate was similar to the slow-pull method and the risk ratio was 1.02 (0.98–1.07) [36]. Moreover, there is no report to date that wet suction is superior to dry suction or the slow-pull method in terms of specimen volume when genomic testing is taken into consideration. In terms of specimen volume with a view of CGP analysis, whether wet or dry suction is better may be an issue for future studies. The primary endpoint of this study is the comparison of the rate of primary and metastatic lesions that met the criteria of the NOP analysis, and as long as the same slow-pull method of negative pressure is applied to both groups, the fact that wet suction is not applied will not affect the primary endpoint.

Finally, double blinding is not possible. The physician naturally knows whether to puncture the primary lesion or the metastatic lesion, which can be a confounding factor. However, despite these limitations, there have been few reports on whether primary lesions or metastatic lesions are more appropriate for collecting specimens for CGP analysis, and this study may provide significant evidence.

